### Data management {19}

Investigators will collect data on participants’ baseline status and daily after randomization. All data obtained will be stored electronically in a securely accessible database and kept strictly confidential. The data transfer process will encrypt and any personally identifiable information will be deleted. De-identification of the data for analysis was allowed only during the final phase of this trial.

Registered participants will be withdrawn from the study if (1) the participant withdraws his/her consent and (2) the exclusion criteria is discovered after registration. The date and reason of the suspension will be recorded, and their data will not be retained.

### Confidentiality {27}

All personal data of registered participants will be assigned a unique identifier and stored on a secure server available only to researchers with administrative privileges. After the trial, only non-personal data will be available for analysis in the data repository.

### Plans for collection, laboratory evaluation, and storage of biological specimens for genetic or molecular analysis in this trial/future use {33}

Not applicable; no biological specimens will be collected.

## Statistical methods

### Statistical methods for primary and secondary outcomes {20a}

Analysis of baseline characteristics of the three groups will be summarized by appropriate descriptive statistics. Analysis of both the primary and secondary outcomes will be performed blinded to treatment assignment and analyzed on the intention-to-treat approach [22], with all randomized participants retaining their original randomization group. If these missing data are judged to be random, multiple imputations of the chained equation will be used to address missing data caused by lost access and non-response.

Normally distributed data were expressed as the mean (standard deviation), whereas data not normally distributed was expressed as the median (interquartile range). The independent sample test was used for the comparison between groups, and the paired sample test was used for the comparison within the group before and after treatment. For clinical symptoms, variables were expressed as percentages. A *χ*^2^ test or Fisher’s exact test was used to compare categorical data. The conventional level of 0.05 for statistical significance was adopted to evaluate the *p*-values. Statistical analysis was carried out by using SPSS software, version 26.

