## Outcomes {12}

### Primary outcome

The primary outcome measure will be the difference in the extent of absorption and dissipation of lung inflammation on CT images. Result comparisons will be made between the test group and the control group and between the LIPUS-treated and non-treated areas within the self-control group.

Pulmonary inflammation on CT images will be assessed by an expert chest radiologist before and 7 days after treatment to compare the area and volume of inflammation in the target area of the lung, as well as the area absorption rate (AAR) or volume absorption rate (VAR). A Pair software will be used to mark and 3D reconstruct the target area of CT images and record the data of pulmonary inflammation changes. AAR is defined as [(target site inflammation area before treatment − target site inflammation area after treatment)/target site inflammation area before treatment] × 100 (%). VAR is defined as [(target site inflammation volume before treatment − target site inflammation volume after treatment)/target site inflammation volume before treatment] × 100 (%).

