### Sample size {14}

Sample size and power calculation are based on the primary outcomes. All sample size calculations assume two-sided analysis with a power of 90% (1-*β* = 0.90) at a significant level of *α* = 0.05. The use of therapeutic LIPUS in viral pneumonia has not yet been reported. Based on the time span of this clinical trial and the number of patients expected to meet the inclusion criteria in our hospital, it is estimated that a total of 66 participants will be required (1:1:1 allocation ratio). We anticipate minimal missing data (< 5%) for the primary outcome (day 7 pulmonary inflammation on CT images) because participants were all inpatients and we have daily contact with them during the treatment phase. With a dropout rate of approximately 5%, a final sample size of 70 participants is required.

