## Data collection and management

### Plans for assessment and collection of outcomes {18a}

The primary outcome data will be collected at the baseline and the termination of treatment; the secondary outcomes will be collected at pre-randomization, a fixed time every day and/or after 7 days of treatment. All variables in the protocol will be documented in an encrypted Microsoft Office Excel. The investigators who enter information into the office excel are responsible for ensuring the accuracy and completeness of information. A day-to-day management group, consisting of the principal investigator, a doctoral student, a research coordinator and an assistant manager, conducts clinical monitoring activities.

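### The LIPUS-versus-control comparison uses an unadjusted test although baseline CT volume is available for everyone; this is valid but can lose power, by an amount the protocol does not allow to be fixed

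*Protocol article*

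**What the plan says.** The protocol article, under Statistical methods for primary and secondary outcomes {20a}, gives the rule for comparing arms: "The independent sample test was used for the comparison between groups". The other rule for continuous data in that section, "the paired sample test was used for the comparison within the group before and after treatment", looks at change inside one arm and does not compare arms. No baseline covariate is named for any analysis.

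Under Primary outcome, inflammation on CT "will be assessed by an expert chest radiologist before and 7 days after treatment to compare the area and volume of inflammation", "as well as the area absorption rate (AAR) or volume absorption rate (VAR". VAR is the difference between the volumes before and after treatment, divided by the volume before; its formula ends with "target site inflammation volume after treatment)/target site inflammation volume before treatment] × 100". Section {18a} confirms the timing: "The primary outcome data will be collected at the baseline and the termination of treatment". So the baseline measurement exists for every participant.

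The Sample size section gives 66 participants at 1:1:1, raised to 70 for dropout. It states no effect size, standard deviation or correlation. The abstract gives 60.

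**The concern.** Expressing the outcome as a percentage of baseline may look like baseline adjustment, but it is not. If day-7 volume does not rise in strict proportion to baseline volume, the percentage still depends on where the patient started, and a chance imbalance in lesion size between two small arms carries into the comparison.

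The ratio is also skewed. Complete clearing scores +100%, while a lesion that grows from 10 to 40 mL scores (10 − 40)/10 × 100 = −300%. The eligibility criteria set no minimum lesion size, and the allocation section mentions no stratification by lesion extent, so nothing stated rules out small denominators or limits imbalance. If the test compares means, one or two patients who progress can weigh heavily.

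What is at stake is precision in a trial whose size was set by feasibility. The covariate that could recover it is already being collected.

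**Working it through.** **Arm size.** 66/3 = 22 per arm. The inflation reproduces: 66/0.95 = 69.5, so 70, or 23.3 per arm. The abstract's 60 gives 20 per arm. The 66 itself cannot be reproduced, because no effect size or SD is given. At 22 per arm, 90% power and two-sided 0.05, the detectable difference is (1.960 + 1.282) × √(2/22) = 0.977 SD of whichever variable is tested.

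**Assumptions, none of them in the protocol.** Volumes are log-normal with log SD 0.8 at both times. The true effect is 0.8 SD of log volume. The baseline to day-7 correlation r of log volume runs from 0.3 to 0.85.

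**Why the ratio still depends on baseline.** With equal SDs, the log ratio of day-7 to baseline volume correlates with log baseline at −√((1 − r)/2): −0.59 at r = 0.3, −0.50 at 0.5, −0.39 at 0.7.

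**Closed-form check on the log scale**, power ≈ Φ(d√(22/2) − 1.96):

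- Unadjusted log ratio: d = 0.8/√(2(1 − r)) = 0.676, 0.800 and 1.033 at r = 0.3, 0.5 and 0.7. Power is 61, 76 and 93%.
- ANCOVA on log volume: d = 0.8/√(1 − r²) = 0.839, 0.924 and 1.120. Power is 79, 87 and 96%.

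The normal approximation runs 1 to 3 points above the simulation below.

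**Simulated power (%), 22 per arm, several thousand trials per setting; repeat runs agree to about a point or two:**

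| r | t-test on VAR | Mann-Whitney on VAR | VAR with log-baseline covariate | t-test on log ratio | ANCOVA, log volume | ANCOVA, cube-root volume |
|---|---|---|---|---|---|---|
| 0.3 | 43 | 57 | 55 | 60 | 76 | 75 |
| 0.5 | 62 | 71 | 69 | 74 | 84 | 83 |
| 0.7 | 86 | 90 | 90 | 92 | 94 | 94 |
| 0.85 | 99.3 | 99.6 | 99.6 | 99.7 | 99.8 | 99.7 |

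With no true effect, all of these tests reject in about 4 to 6% of trials, the unadjusted ones included.

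**Splitting the gain at r = 0.5.** Keeping VAR and adding the covariate moves 62% to 69%. Changing only the scale (log ratio, no covariate) moves 62% to 74%, and the covariate then adds the step to 84%. Both changes contribute.

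**Least favourable case.** Let day-7 volume be proportional to baseline, with noise independent of baseline (SD 0.4 to 0.8 on the log scale) and an effect of 0.8 noise SD. Power is then 62 to 70% for the t-test on VAR, 71 to 72% for Mann-Whitney, 72 to 73% for log ANCOVA and 68 to 70% for cube-root ANCOVA. Against Mann-Whitney there is practically no gain, and the cube-root model is about 2 to 4 points lower.

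Log-normal volumes contain no zeros, so complete clearing is not represented in these runs.

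**The case against.** A reader might infer that the plan throws away a definite amount of power. The documents do not support that. They give no SD, effect size or correlation, and the loss in the table follows from assuming equal log SDs with a correlation below 1. At 0.85, or under proportionality when compared with Mann-Whitney, it all but disappears. This objection stands in full against any single figure.

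A reader might also infer that a t-test on VAR is fixed. It is not. Section {20a} names only an independent-sample test and provides for medians when data are not normal, so a rank test is a fair reading, and it resists the outliers described above. Raw area and volume are listed beside the absorption rates, and the section does not say which is tested. The argument about means therefore applies only if means are compared. Choosing raw day-7 volume instead would not help, since an unadjusted test of it makes no use of baseline at all.

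Nor is the unadjusted test wrong. Randomisation protects its type I error, so this is a question of efficiency.

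Finally, covariates are often left to an analysis plan, and one may exist unseen. But the article does state a between-group method, and that stated method is what this point addresses.

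**Conclusion.** The point holds as a recommended improvement. The stated test between LIPUS and control is unadjusted, the baseline volume is available for everyone, and dividing by it does not replace adjusting for it.

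Under the assumptions shown, ANCOVA on log volume gains about 8 to 33 points over a t-test on VAR (94 − 86 to 76 − 43) and about 4 to 19 over Mann-Whitney (94 − 90 to 76 − 57) for correlations from 0.7 down to 0.3. The gain falls to practically nothing in the favourable cases described. Part of it belongs to the change of scale. The true size cannot be settled from the protocol, and that is itself a reason to prefer a method whose performance depends less on the unknown correlation. Using 20 or 23 per arm instead of 22 does not alter this.

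The comparison of treated with non-treated areas in the self-control group is within patients and is not covered.

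**What to change.** Name one primary analysis for LIPUS versus control: ANCOVA of day-7 inflamed volume on the cube-root scale, with cube-root baseline volume as covariate. The cube root allows a volume of zero, which the log does not. Report VAR descriptively for each arm, and give rank ANCOVA of VAR on baseline volume as a sensitivity analysis. Use the baseline value as covariate for continuous secondary outcomes measured before and after treatment. Fix this in writing before unblinding. For this comparison it also settles which of the listed CT measures is tested.

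The cost is analysis wording only: no extra patients or scans, and the SPSS version already named can run it. There are two small downsides. The estimate is less direct than a difference in percentages, which is why VAR stays in the report. And if day-7 volume is exactly proportional to baseline, power can be about 2 to 4 points below Mann-Whitney on VAR.

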### Interim analyses {21b}

No interim analyses will be planned.

### Methods for additional analyses (e.g., subgroup analyses) {20b}

No any subgroup analysis will be conducted.

### Methods in analysis to handle protocol non-adherence and any statistical methods to handle missing data {20c}

We anticipate minimal missing data (< 5%) for the primary outcome (day 7 pulmonary inflammation on CT images) because participants were all inpatients and we have daily contact with them during the treatment phase. We will evaluate the impact of missing data by calculating the difference across plausible and extreme missing data scenarios. If our primary test is significant, we will also calculate the size of the interaction between the group and missingness required to make this difference non-significant. If 10% or more of the baseline samples are excluded due to missing data, we will use multiple imputation techniques for analysis.

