### Criteria for discontinuing or modifying allocated interventions {11b}

Patients are free to withdraw from participation in the study at any time upon request, without any consequence. If a participant chooses to discontinue the study intervention, we will not collect or use their data.

LIPUS is an FDA-approved and safe treatment modality. To date, no adverse events have been reported with the low-power LIPUS regimen in soft tissue. Therefore, we anticipate that the risk to the safety of participants will be minimal. However, nursing staff will still monitor potential mild adverse reactions such as mild local swelling, spotting bleeding, enhanced local pain response, and local hyperesthesia or decrease. In case of corresponding symptoms, appropriate symptomatic treatment shall be carried out. Regardless, participants can withdraw from the study at any time if they experience adverse events that are unacceptable to them.

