### Plans to promote participant retention and complete follow-up {18b}

The patients will complete all evaluations and treatments during hospitalization. Lung CT examinations, ultrasound examinations, and trial-related laboratory examinations received by patients before and after treatment are provided free of charge. Once a patient withdraws from the study during treatment (does not complete the full 7-day treatment period), their data will not be retained. Every effort should be made to encourage patients to remain in the study for the duration of their planned outcome assessments.

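### Sections {20a} and {20c} set different triggers for imputing a missing day-7 CT and the withdrawal rules add a third, so the primary analysis depends on which section is followed

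*Protocol article*

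**What the plan says.** The protocol article deals with a patient who has no day-7 CT in several places.

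- **Statistical methods {20a}**: outcomes are "analyzed on the intention-to-treat approach [22], with all randomized participants retaining their original randomization group". On imputation: "If these missing data are judged to be random, multiple imputations of the chained equation will be used to address missing data". No percentage is attached.
- **Missing data {20c}**: "If 10% or more of the baseline samples are excluded due to missing data, we will use multiple imputation techniques for analysis". No condition on the mechanism is attached, and no arm or comparison is named for the 10%. The same section says "We anticipate minimal missing data (< 5%) for the primary outcome (day 7 pulmonary inflammation on CT images"). It also plans sensitivity work: "We will evaluate the impact of missing data by calculating the difference across plausible and extreme missing data scenarios". If the primary test is significant, it adds a calculation of how strong a group-by-missingness interaction would have to be to overturn the result.
- **Discontinuation {11b}**: "If a participant chooses to discontinue the study intervention, we will not collect or use their data".
- **Retention {18b}**: "Once a patient withdraws from the study during treatment (does not complete the full 7-day treatment period), their data will not be retained".
- **Data management {19}**: for withdrawn consent, or an exclusion criterion found after registration, the date and reason are recorded but the data are not kept.
- **Sample size {14}**: "it is estimated that a total of 66 participants will be required (1:1:1 allocation ratio"), raised to 70 for about 5% dropout. The abstract gives 60.

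**The concern.** Sections {20a} and {20c} both say when the primary outcome will be imputed, and their conditions differ in kind: a judgement about mechanism in one, a count in the other. Two analysts, each following one section faithfully, could produce different primary analyses from the same data. The withdrawal rules then remove some randomised patients before either condition is reached.

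This matters because the trial is small, at about 22 per arm, so a few patients kept or dropped can shift an arm mean. A percentage pooled over arms also cannot detect loss that falls mainly in one arm, and uneven loss is the pattern most likely to bias a comparison between arms. Leaving the choice open until analysis adds discretion over the main result.

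**Working it through.** **1. The two imputation rules side by side**

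| Missing day-7 CT | {20a} | {20c} |
|---|---|---|
| Under 10%, judged random | impute | not imputed |
| Under 10%, not judged random | not imputed | not imputed |
| 10% or more, judged random | impute | impute |
| 10% or more, not judged random | not imputed | impute |

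The rules differ in the first and last rows. With under 5% expected, the first row is the one to plan for if missingness is judged random. There {20a} keeps the patient by imputation, and {20c} leaves the patient excluded.

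**2. The plan's own figure.** 66/0.95 = 69.5, which rounds up to 70, so the stated final size is reproduced. The 66 itself cannot be reproduced because no effect size or SD is given, but nothing below needs one.

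**3. How much loss stays below the trigger.** Assume that the 10% is counted over all participants. This is the plain reading, but the section does not say so. Take the largest whole number k with k/N < 0.10, then divide by the arm size. Do the same for the expected bound, k/N < 0.05.

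| N (source) | Arm | Largest k below 10% | k/arm | Largest k below 5% | k/arm |
|---|---|---|---|---|---|
| 66 ({14}) | 22 | 6 (9.1%) | 27.3% | 3 (4.5%) | 13.6% |
| 70 ({14}) | 23 | 6 (8.6%) | 26.1% | 3 (4.3%) | 13.0% |
| 70 ({14}) | 24 | 6 (8.6%) | 25.0% | 3 (4.3%) | 12.5% |
| 60 (abstract) | 20 | 5 (8.3%) | 25.0% | 2 (3.3%) | 10.0% |

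The k/arm columns are worst cases, with every loss in a single arm.

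**4. Other denominators at 22 per arm.** Counted over the two parallel arms only, the most is 4/44 = 9.1% overall, or 4/22 = 18.2% of one arm. Counted per arm, it is 2/22 = 9.1%.

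**5. How unusual the worst case is.** If six losses at N = 66 fell at random, the chance that all are in the same arm is 3 × C(22,6)/C(66,6) = 3 × 74,613/90,858,768 = 0.0025, about 0.25%.

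**6. The third rule.** Take a patient who stops on day 3 and has no day-7 CT. Section {20a} alone would keep the patient and impute if the loss is judged random. Section {20c} alone would exclude the patient unless the 10% is reached. Sections {11b} and {18b} discard the patient's data, so the baseline CT and the daily SaO2 and rales records are not there to impute from. Reconciling {20a} with {20c} alone would therefore settle the matter only for patients who complete treatment but lack a usable CT.

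**The case against.** The strongest reply is that little data will be missing. Patients are inpatients seen daily, and at under 5% missing the choice of method may change little. Section {20c} also already plans scenario analyses at any percentage and, for a significant result, a tipping-point calculation on group by missingness, which addresses loss related to arm. Much of this stands: the sensitivity plan is good and should stay. But it does not say which rule produces the primary estimate, and the tipping-point step applies only after a significant test.

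The two sections could also be read together, with imputation only if loss is both random and at least 10%. Neither section says this. At the expected loss it would still leave complete cases as the default, against the intention-to-treat statement.

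A reader might infer three stronger things that the documents do not support.

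- *That over a quarter of an arm will be lost unimputed.* This needs a pooled denominator and every loss in one arm. It is exactly 25.0% at N = 60 or in a 24-patient arm, and lower under the other denominators.
- *That the trigger costs 0.27 SD of bias.* If six leavers from an arm of 22 had done 1 SD worse than the others (an assumption), the complete-case mean would be off by 6/22 × 1 SD = 0.27 SD. Imputation removes that only as far as recorded data predict the missing CT, so it is not a measured cost of the trigger.
- *That device-related leaving is confined to sonicated patients.* Under {11a} controls wear the apparatus too; only effects of sonication itself are confined, and two arms receive it. If six losses split evenly between those arms, each loses 3/22 = 13.6%. Losses in the self-control arm bear on its within-patient comparison, not on test versus control.

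**Conclusion.** The contradiction is real and does not depend on any numerical assumption. Sections {20a} and {20c} give different conditions for imputing the primary outcome, and they part company at the level of loss that the protocol expects. Sections {11b}, {18b} and {19} add a rule that contradicts {20a} and takes away the data imputation would use. These are stated rules in conflict, not detail left to an analysis plan.

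The likely size is modest: at the expected loss, at most 3 of 22 in an arm. The upper limit of 25% to 27% of an arm holds only if the 10% is counted over the whole trial and all losses fall in one arm. The case for change rests on the ambiguity over the primary analysis, not on that extreme. It should be settled before the data are analysed.

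**What to change.** - Delete the 10% trigger in {20c} and state one rule in {20a} and {20c}: all randomised participants are in the primary analysis, and a missing day-7 CT is imputed by arm whatever the percentage. Use the baseline CT and the daily SaO2 and rales records that the Outcomes section already schedules.
- Reconcile {11b}, {18b} and {19} with this, so that data collected before a patient stops are retained and used as far as consent allows. Without this step the imputation rule cannot be applied to leavers.
- Keep {20c}'s scenario analyses and its group-by-missingness calculation as the sensitivity analysis for non-random loss, and let the scenarios differ by arm. A judgement that data are missing at random then no longer decides whether a patient is counted.

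The cost is wording in about five places and a little more analysis. No new measurements are needed, but records that the present text would discard must be kept.
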